**Methods/Design:**

The study will be conducted as a clinical, multicentre, randomised controlled trial with balanced randomisation (1:1). The planned sample size is 208 participants (at 1:1 ratio, 104 subjects in each group). At 5–7 days after RH III, patients are screened according to operative and pathological findings. Enrolled participants are randomised into an intervention group (TENS plus conventional clinical care) or control group (conventional clinical care), with stratification by menopausal status (menopause vs. non-menopause) and surgical modality (laparoscopic RH or abdominal RH). Participants in both groups will be followed up at 14 days, 21 days, 28 days, 3 months, 6 months, 12 months, 18 months and 24 months after surgery. The primary endpoint is improvement rate of urination function which is defined as recovery (residual urine ≤50 ml) or improvement (residual urine 50–100 ml). Secondary endpoints include urodynamic parameter, urinary incontinence, anorectal function, pelvic function, quality of life (QOL), disease-free survival and adverse events. Primary endpoint analyses will be carried out by Cochran-Mantel-Haenszel tests taking into center effect.

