## Background

Cervical cancer is one of the most commonly diagnosed malignant tumors among women all over the world [1]. There are an estimated 131.5 thousand newly diagnosed cervical cancer cases per year in China, accounting for 28.8% of the world’s cases. In all, 30% of cervical cancer patients are younger than 30 years [2]. With the widespread availability of cervical cancer screening, the proportion of early stage cervical cancer is increasing year by year. The standard treatment for patients with early stage cervical cancer is class III radical hysterectomy plus pelvic lymphadenectomy, with chemotherapy and/or radiotherapy supplemented as needed. The 5 year survival rate after treatment can reach as high as 90% [2]. Pelvic vessels, autonomic nerve fibers and ligaments could be affected by the resection of anterior, lateral and posterior parametrium and vaginal cuff. The unintended interruption may result in pelvic floor dysfunction including disorders of lower urinary tract, defecation disorders and sexual dysfunction. Though the cancer could be cured by the surgery, many patients may suffer from decreased quality of life due to the poor pelvic function following radical hysterectomy.

It has been reported that 70%–85% cervical cancer patients suffer from bladder dysfunction following radical hysterectomy [3, 4]. The main symptom of short-term bladder dysfunction is urinary retention (UR) while the long-term postoperative bladder disorder is urinary incontinence [5, 6]. Usually the time of indwelling urinary catheter after class III radical hysterectomy is 2 weeks, but it lasts up to 1 month in about 15% patients and even more than half a year in 3% patients because of chronic urinary retention [6, 7].

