### Study endpoints

The primary endpoint is improvement rate of urination function. Based on self-urination status and residual urine evaluated by B ultrasound following catheter removal and self-urination, efficacy is classified into three levels: 1) recovery: automatic micturition is achieved by patients with residual urine ≤50 ml; 2) improvement: automatic micturition is achieved by patients with residual urine 50–100 ml; 3) invalid: automatic micturition is not achieved, or automatic micturition is achieved but with residual urine ≥100 ml. Improvement rate is calculated as follows: (the number of recovery participants + the number of improvement participants)/the total number of enrolled participants *100%.

Secondary endpoints are: (1) urodynamic parameter, including maximal uroflowmetry, micturition curve, bladder sensation, detrusor muscle stability, detrusor muscle function of contraction, stress urinary incontinence, urinary retention and lower urinary tract obstruction; (2) urinary incontinence evaluated by 1 h pad test is defined as follows: <1 g continence, 1–10 g mild incontinence, 11-30 g moderate incontinence, 31-50 g severe incontinence, >50 g extremely severe incontinence; (3) anorectal function, including rectal sensation, rectal maximum volume, reflex of rectal anal internal sphincter, reflex of rectal anal external sphincter and balloon expulsion testing; (4) pelvic function, including muscle strength of type I and type II muscle fiber of pelvic muscle, fatigue of pelvic muscle, vaginal dynamic pressure and neural reflex; (5) QOL evaluated by EQ-5D, PISQ-12, PFDI-20 and ICIQ/OABss; (6) overall survival (OS), calculated as the time from initial diagnosis to death from any cause or the date of last follow-up for surviving subjects; (7) disease-free survival (DFS), defined as the period from the date of initial diagnosis to the date of recurrence, metastasis, death due to any cause or the date of last follow-up for surviving subjects; (8) adverse events.

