### Sample size consideration

We expect improvement rate of urination function 70% in the intervention group and 50% in the control group. Based on a difference of 20% between groups on the primary outcome, assuming 10% drop-out rate, a total of 208 participants (at 1:1 ratio, 104 subjects in each group) are required to provide 80% power, with the use of two-sided significance level of 0.05.

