### Statistical analysis

Analyses will be made using SAS statistical software (version 9.3) by a statistician in Peking University Clinical Research Institute. Data will be analyzed according to the “intent-to-treat” principle. A two-sided significance level of 5% will be used for all analyses.

Descriptive statistics will be used to summarize demographic and clinical characteristics of participants randomised to the intervention and control groups. The difference between two groups on demographic characteristics, socioeconomic status, clinical characteristics and follow-up retention rate will compared using t-tests (or Wilcoxon rank sum test) and chi-square test/Fisher’s exact test as appropriate.

Primary outcome (improvement rate of urination function in 1 year) analyses will be carried out by Cochran-Mantel-Haenszel tests taking into center effect.

The difference in urodynamic parameter, anorectal function and pelvic function between intervention and control groups will be determined using t-tests or Wilcoxon rank sum tests as appropriate. The severity of urinary incontinence will be analyzed using the Wilcoxon rank sum test. The differences in QOL (evaluated by EQ-5D, PISQ-12, PFDI-20 and ICIQ/OABss) between intervention and control group will be determined using repeated measure analysis of variance (ANOVA). DFS and OS survival curves will be calculated using the Kaplan-Meier method, and compared using the log-rank test. Cox proportional hazards models will also be used to calculate hazard ratio and 95% confidence interval, with other risk factors (such as cancer stage and tumor localization) as covariates.

The incidence of adverse events between 2 groups will be compared with the chi-square test/Fisher’s exact test. Descriptive statistics will be used to summarize incidence rates of adverse events and serious adverse events.

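### OS and DFS are counted from initial diagnosis rather than randomisation, and the supplementary adjusted Cox model for OS has more parameters than the expected deaths can support

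*Protocol article*

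**What the plan says.** Under Study endpoints, the protocol article lists "overall survival (OS), calculated as the time from initial diagnosis to death from any cause or the date of last follow-up for surviving subjects" and "disease-free survival (DFS), defined as the period from the date of initial diagnosis to the date of recurrence, metastasis, death due to any cause" as secondary endpoints. In both, surviving women are censored at last follow-up.

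Entry to the trial comes later than diagnosis. The abstract states: "At 5–7 days after RH III, patients are screened according to operative and pathological findings". The inclusion criteria require a completed class III radical hysterectomy, negative nodes and margins, and no distant metastasis. Follow-up ends 24 months after surgery.

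Under Statistical analysis, OS and DFS are described by Kaplan-Meier and compared by the log-rank test. Cox models are an addition, giving a hazard ratio and 95% confidence interval "with other risk factors (such as cancer stage and tumor localization) as covariates". A two-sided 5% level applies to all analyses. The sample size rests on urination function alone, and no expected number of OS or DFS events is given.

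**The concern.** There are two separate issues.

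**Time origin.** A woman who died, or whose disease proved metastatic, between diagnosis and the postoperative screen could not be enrolled. The interval from diagnosis to randomisation is therefore event-free by design, differs between women, and has nothing to do with the allocated arm. Counting it makes the survival curves look better than survival under follow-up in the trial. For DFS the definition also fails on its own terms, since a woman is not disease-free before her tumour is removed.

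**Adjusted model.** The covariates are given as examples, so the list is open, while few deaths can be expected among low-risk patients in two years. An adjusted hazard ratio resting on two or three deaths per parameter is unstable.

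The article's Discussion calls the safety of TENS in cancer patients uncertain. OS and DFS are the trial's defined cancer-control endpoints, so readers will look to them for reassurance. A non-significant result could then be taken for more than it is.

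**Working it through.** **The plan's own figure.** The sample size follows from 70% vs 50%, 80% power, two-sided 0.05 and 10% drop-out. With pooled variance:

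n = [1.96·√(2·0.6·0.4) + 0.8416·√(0.7·0.3 + 0.5·0.5)]² / 0.2² = (1.358 + 0.571)² / 0.04 ≈ 93 per arm

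93 / 0.9 = 103.3, rounded up to 104, so 208 in total. The stated size reproduces exactly.

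**Expected deaths.** The inputs are N = 208, follow-up of 24 months, and five-year survival of about 90% (abstract and Background). A constant hazard is assumed.

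- Hazard: −ln(0.90)/5 = 0.0211 per year
- Two-year death probability: 1 − 0.9^(2/5) = 4.13%
- Deaths: 208 × 0.0413 = 8.6. With 187 completers: 7.7. If the 10% who drop out leave at one year: 8.2.

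| Five-year survival | Deaths, N = 208 | Deaths, 187 completers |
|---|---|---|
| 85% (assumed) | 13.1 | 11.8 |
| 90% (article) | 8.6 | 7.7 |
| 95% (assumed) | 4.2 | 3.8 |

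The 90% figure describes early-stage patients in general. This trial selects for low risk, so the count may be lower.

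**Deaths per parameter (OS).** Treatment takes 1, stage 2 (three FIGO levels, if categorical) and localisation at least 1, so at least 4 parameters: 8.6/4 ≈ 2.1. With stage as a single term there are 3: 8.6/3 ≈ 2.9, or 8/3 ≈ 2.7. In a simulation with an assumed 20/65/15 stage mix, some stage level had no deaths in about 40% of trials. Its coefficient could not then be estimated.

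**Precision without any adjustment (OS).** SE(log HR) = 2/√8.6 = 0.68, so the 95% interval around HR = 1 is exp(±1.96 × 0.68), about 0.26 to 3.8. By Schoenfeld's formula with 8.6 deaths, power for HR 2 is Φ(0.693 × √8.6/2 − 1.96) = Φ(−0.94) ≈ 17%; 80% power needs 66 events. If TENS truly doubled the hazard there would be more deaths (12.7 on average in simulation), and the simulated rejection rate was about 22%.

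**Size of the time-origin effect.** The article gives no interval from diagnosis to randomisation, so a lag must be assumed.

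*Absolute survival at 24 months*, as exp(−h × (2 − lag)):

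| Lag | 24-month OS |
|---|---|
| 0 (from randomisation) | 95.9% |
| 1 month | 96.0% |
| 2 months | 96.2% |
| 3 months | 96.4% |

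*Between-arm comparison*, from 2,000 simulated trials of 208 women per scenario, with a varying lag averaging about 1.4 months:

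| | From randomisation | From diagnosis |
|---|---|---|
| Log-rank rejection, true HR 1 | 4.1% | 4.3% |
| Average estimated HR, true HR 2 | 2.145 | 2.146 |

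**The case against.** The strongest reply is that neither issue touches the main comparison. Much of that reply stands.

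- **A reader might infer that lead time biases the treatment effect.** The documents do not support this. The lag arises before allocation and randomisation balances it; the simulation shows essentially no change in type I error or hazard ratio.
- **A reader might infer that the whole survival comparison is overfitted.** It is not. The arms are compared by an unadjusted log-rank test, and the Cox model is additional. Only the adjusted hazard ratio is affected.
- **A reader might apply the figure of about 8 events to DFS.** It counts deaths only. DFS also counts recurrence and metastasis, and no rate is given for these. DFS is also the only one of the two that the abstract lists.
- **A reader might treat low power for OS as a design error.** It is not one in a trial sized on urination function. Nor do the endpoint and analysis sections designate OS or DFS as a formal safety test. Tumour markers, gynaecological examination, chest X-ray and adverse events are also followed to 24 months, so OS and DFS are not the only information on cancer control.

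It is also fair to say that final covariates and their coding may be settled in a document not shown. The article nevertheless commits to adjustment, names stage and localisation, and fixes the time origin. Those statements can be judged as they stand.

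**Conclusion.** The point holds in a limited form. Starting OS and DFS at diagnosis is a definitional error, and for DFS an illogical one. Its effect is a slight inflation of absolute survival in both arms: 0.1 to 0.5 percentage points at 24 months for an assumed 1 to 3 month lag. It does not materially bias the log-rank test or the hazard ratio.

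The adjusted Cox model cannot be supported for OS. Even the upper assumed count of 13 deaths gives only 13.1/4 ≈ 3.3 per parameter with four parameters, and the lower count of about 4 gives roughly one. This rests on a constant hazard, the article's general 90% figure and the parameter count shown above. Whether the same holds for DFS cannot be determined from the article.

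**What to change.** 1. Define OS and DFS from the date of randomisation. The date of diagnosis can still be reported as a baseline characteristic.
2. Keep Kaplan-Meier and the log-rank test as planned.
3. Make the Cox hazard ratio treatment-only, or Firth-penalised, when events are few. State in advance the event count at which this applies, and apply it to OS and DFS separately.
4. Report OS and DFS hazard ratios with 95% confidence intervals as descriptive, with a sentence that a non-significant difference does not show oncological safety.

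The cost is a few sentences and one changed start date in the derivation. Allocation runs through a central web-based system, so the randomisation date should already be on record. No new data, visits or participants are needed.

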### Sample size consideration

We expect improvement rate of urination function 70% in the intervention group and 50% in the control group. Based on a difference of 20% between groups on the primary outcome, assuming 10% drop-out rate, a total of 208 participants (at 1:1 ratio, 104 subjects in each group) are required to provide 80% power, with the use of two-sided significance level of 0.05.

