### Initial screening, assessment and follow-up

After providing informed consent, participants are asked standardized questions about their demographic characteristics, socioeconomic status and medical history. Clinical data is extracted from the medical records regarding primary tumor, time of primary diagnosis, surgical operation, physical examination, laboratory testing, gynecological examination and imaging examination (Table 1).

**Table 1 Tab1:** Baseline screening, assessment, and follow-up schedule

	At baseline	Time after surgery								Early withdrawal
		14 days	21 days	28 days	3 months	6 months	12 months	18 months	24 months	
Follow-up time window (days)		±2	±2	±2	±7	±7	±7	±7	±7	
Informed consent	●									
Demographic characteristics	●									
Socioeconomic status	●									
Medical history	●									
Information on tumor clinical evaluation and surgical operation	●									
Physical examination	●									
Blood routine examination	●				●	●	●	●	●	
Blood clotting function	●									
Routine urine test	●				●	●	●	●	●	
Routine stool test	●				●	●	●	●	●	
Blood biochemistry	●				●	●	●	●	●	
Hormone testing^a^	●				●	●	●	●	●	●
Tumor biomarkers^b^	●				●	●	●	●	●	●
Gynecological examination^c^	●				●	●	●	●	●	●
Abdominal/pelvic CT/MRI	●	▲								
Chess X-ray	●					●	●	●	●	●
Randomization	●									
Assessment of residual urine^d^		●	●	●	●	●	●			
Uroflowmetry				●	●					
Urodynamic tests				●						
Anorectal function evaluation				●						
Pelvic floor functional testing				●	●					
EQ-5D^e^					●	●	●		●	
PISQ-12^f^						●	●		●	
PFDI-20^g^					●	●	●		●	
ICIQ/OABss^h^					●	●	●		●	
Adverse events	●				●	●	●	●	●	●

●: Indicates mandatory items

▲: Investigator will decide whether to perform the testi according to clinical signs or clinical evaluation

^a^Hormone testing includes estradiol, progesterone, testosterone, prolactin, follotropin and luteinizing hormone

^b^Tumor biomarkers includes squamous cell carcinoma antigen, CA125, CA199 and carcinoembryonic antigen

^c^Gynecological examination includes Human Papillomavirus and Thinprep Cytological Testing

^d^Residual urine is evaluated by B ultrasound

^e^EQ-5D: European Quality of Life-5 Dimensions

^f^PISQ-12: Prolapse/Urinary Incontinence Sexual Questionnaire short form

^g^PFDI-20: Pelvic Floor Distress Inventory

^h^ICIQ/OABss: International Consultation on Incontinence Questionnaire/Overactive Bladder Symptom Score

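### The sample size takes drop-outs out of the analysis while the endpoint formula keeps them in, so the stated 80% power does not match the endpoint; 208 women give about 74% to 84%, depending on points the article leaves open

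*Protocol article*

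**What the plan says.** Three sections of the protocol article bear on this.

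- **Sample size consideration.** The planning rates are "We expect improvement rate of urination function 70% in the intervention group and 50% in the control group". The size is set "Based on a difference of 20% between groups on the primary outcome", and the result is stated as "assuming 10% drop-out rate, a total of 208 participants (at 1:1 ratio, 104 subjects in each group) are required to provide 80% power", at a two-sided 0.05 level.
- **Study endpoints.** The improvement rate is defined by an explicit fraction: ("the number of recovery participants + the number of improvement participants)/the total number of enrolled participants *100"%. The denominator is everyone enrolled.
- **Statistical analysis.** "Data will be analyzed according to the “intent-to-treat” principle". The primary comparison is a Cochran-Mantel-Haenszel test allowing for centre. The time frame is given only as one year, with no deciding visit.

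Residual urine is scheduled at 14, 21 and 28 days and at 3, 6 and 12 months (Initial screening, assessment and follow-up, and Table 1).

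**The concern.** An allowance for drop-out of the form n/(1 − d) protects power only if drop-outs are removed from the analysis and the planning rates apply to those who remain. If drop-outs stay in the denominator and cannot enter the numerator, both arms' rates shrink by the same factor, and so does the difference between them. Enrolling more women partly offsets this but does not restore the planned power.

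The article uses the first logic to set the sample size and the second to define the endpoint. What is at stake is how the result is read: a non-significant finding would be judged against an 80% figure that was worked out for a different denominator.

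**Working it through.** **Inputs** (all from the article): p1 = 0.70, p2 = 0.50, two-sided α = 0.05, power 80%, drop-out d = 10%, 104 per arm (Sample size consideration); denominator = all enrolled (Study endpoints).

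**Step 1: reproduce 208.** Pooled two-proportion formula:

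n = [1.960·√(2·p̄·(1−p̄)) + 0.842·√(p1(1−p1) + p2(1−p2))]² / (p1−p2)²

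With p̄ = 0.60: [1.960·√0.48 + 0.842·√0.46]² / 0.04 = 93.0, so 93 per arm. Then 93/0.9 = 103.3, rounded up to 104 per arm, or 208 in total. This is an exact match. The arcsine formula also gives 93 and 104. The unpooled formula gives 91 and 102, and the continuity-corrected one 103 and 115. The 208 is thus the size for 93 women per arm with an outcome, and its arithmetic is correct on those terms.

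**Step 2: move to the all-enrolled denominator.** Let d be the share of enrolled women in each arm who leave without a usable outcome and so add nothing to the numerator. If the rest improve at 70% and 50%, the analysed rates are 0.70(1−d) and 0.50(1−d). At d = 10% these are 0.9 × 70% = 63% and 0.9 × 50% = 45%, a difference of 18 points instead of 20.

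**Step 3: power at 104 per arm.**

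power = Φ{ [(p1−p2)·√n − 1.960·√(2·p̄·(1−p̄))] / √(p1(1−p1) + p2(1−p2)) }

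For 63% vs 45%, p̄ = 0.54: [0.18·√104 − 1.960·√0.4968] / √0.4806 = (1.836 − 1.381)/0.693 = 0.655, and Φ(0.655) = 74.4%. The unpooled formula gives 75.4%; an exact binomial calculation for the chi-square test gives 73.4%.

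| Share of enrolled counted as not improved for want of an outcome | Rates | Power, 104 per arm |
|---|---|---|
| 0% | 70% vs 50% | 84.3% |
| 5% (half of the planned drop-outs) | 66.5% vs 47.5% | 79.5% |
| 10% (all planned drop-outs) | 63% vs 45% | 74.4% |
| 15% (above the planned rate) | 59.5% vs 42.5% | 69.1% |

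In the 0% and 5% rows, drop-outs whose outcome is on record are taken to improve at the planning rates. The 0% row is also the power if 70% and 50% were meant as rates among all enrolled, in which case the division by 0.9 was not needed.

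**Step 4: scale of the gap.** For 80% power at 63% vs 45% the pooled formula gives 119.2, so 120 per arm (240 in total), with no further allowance for drop-out.

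These figures ignore stratification by centre in the Cochran-Mantel-Haenszel test.

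**The case against.** The strongest reply is that the article never says a missing outcome counts as failure. Intent-to-treat alone does not imply it, and the lowest efficacy category requires either failure to void or a high residual volume, neither of which is known for a woman with no reading. The rule for missing outcomes may stand in an analysis plan that is not shown. This stands as a limit on the size of the effect. It does not remove the mismatch: the article itself fixes the denominator as all enrolled, and the sample size was derived as if it were not.

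Timing is the second reply, and it also stands. Half of the six residual-urine readings fall in the first month. If the one-year endpoint counts improvement at any visit up to 12 months, a woman recorded as improved at day 21 who leaves at month 6 remains a success. Only if the 12-month reading alone decides would the whole 10% be lost, and the article does not say that.

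Third, the 70% and 50% might already be all-enrolled rates, which puts power above the stated figure. The division by 0.9 makes this less likely, but the text does not exclude it.

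A reader might therefore infer that the trial has 74% power rather than 80%. The documents do not support that as a flat statement, because it needs every planned drop-out, equally in both arms, to leave without a countable success.

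**Conclusion.** The point holds as an inconsistency between the sample size and the endpoint definition, with moderate confidence. It is not an arithmetic error: 208 is right for an analysis of women with an outcome. The stated 80% does not follow from the prescribed all-enrolled endpoint. At the planned 10% drop-out, power with 104 per arm runs from about 74% (all drop-outs counted as not improved, equally in both arms) through about 79% (half of them) to about 84% (none, or planning rates already on the all-enrolled scale).

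Two further inferences go too far. The 240 in the working measures the gap under the least favourable of these cases; it does not show that the trial must enrol more. Table 1 marks no residual-urine reading at early withdrawal, but adding one is not needed to reconcile the text. Such readings would also weaken the premise behind the 74%, because those women would no longer lack a reading.

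**What to change.** In Sample size consideration, restate the power on the all-enrolled scale, for example: *with 104 women per arm, power is about 74% (63% vs 45%) if the 10% who drop out are counted as not improved, and up to about 84% if 70% and 50% hold among all enrolled*.

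Also state:

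- whether 70% and 50% are rates among women with an outcome or among all enrolled;
- which visit, or which rule across visits, decides the one-year primary endpoint.

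With these settled, the range can be reduced to the case that applies, and the power figure will agree with the denominator in Study endpoints. The cost is a few sentences and possibly a less favourable power figure. Enrolment, visits and procedures do not change.
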